# Effects of the Population-Based “10,000 Steps Duesseldorf” Intervention for Promoting Physical Activity in Community-Dwelling Adults: Protocol for a Nonrandomized Controlled Trial

**DOI:** 10.2196/39175

**Published:** 2022-09-21

**Keywords:** physical activity, population-based complex intervention, replication study, multilevel strategy

## Abstract

**Background:**

The World Health Organization recommends 150 minutes of moderate to vigorous physical activity (PA), which translates to approximately 7000 to 10,000 steps per day for adults. In Germany, less than half of the population in this age range meets this recommendation, highlighting the need for population-based intervention approaches for promoting daily PA.

**Objective:**

The complex community-based PA intervention “10,000 Steps Ghent,” which was originally developed in Belgium and was shown to be effective for PA promotion, has been adapted for implementation and evaluation in 2 German cities. The original Belgian study is currently being replicated, and we aim to examine the effectiveness of the adapted intervention among adults living in intervention city districts in Duesseldorf when compared with those living in control city districts in Wuppertal, over the course of 1 year.

**Methods:**

A controlled intervention trial examining the effects of an intervention addressing multiple levels (eg, individual level: website; organizational level: PA promotion in companies; community level: media campaigns and environmental changes) is being conducted. PA and various secondary outcomes will be assessed in 2 random samples of adults aged 25 to 75 years (n=399 in each city) at baseline and after 1 year.

**Results:**

Funding for this study was obtained in March 2020. Recruitment for this study and baseline data collection were conducted from May 2021 to March 2022 (as of March 2022, 626 participants were enrolled in the study). The intervention will be implemented in Duesseldorf for 1 year from April 2022 onward, and follow-up assessments will be conducted, starting in May 2023 (until September 2023). Data analysis will be performed in fall 2023, and the results will be published in spring 2024.

**Conclusions:**

To our knowledge, this is the first research project (currently underway in Germany) that is aimed at replicating the effects of a complex intervention for PA promotion that was previously shown to be effective in another European country.

**Trial Registration:**

German Clinical Trials Register DRKS00024873; https://tinyurl.com/4c9e8azh

**International Registered Report Identifier (IRRID):**

DERR1-10.2196/39175

## Introduction

Physical inactivity is the fourth largest risk factor for mortality worldwide and is one of the main drivers contributing to the etiology of noncommunicable diseases, such as type 2 diabetes, cardiovascular diseases, and certain cancers, which are preventable to a certain extent [1]. In Germany, an estimated 91% of deaths are due to these noncommunicable diseases [2]. It is widely known from previous research that the reduction of an inactive lifestyle [3] and an increase in regular physical activity (PA) leads to improvements in health, including physical, psychological, cognitive, and functional health over the entire life span [3,4]. A recently published cohort study found that among middle-aged men and women walking ≥7000 steps per day was associated with lower mortality rates compared with those walking ≤7000 steps per day [5].

The 2020 update of the recommendations for PA of the World Health Organization (WHO) and the American College of Sports Medicine states that “all adults should undertake 150-300 minutes of moderate-intensity, or 75-150 minutes of vigorous-intensity physical activity, or some equivalent combination of moderate-intensity and vigorous-intensity aerobic physical activity, per week” [6]. It has been noted that 150 minutes per week is the equivalent of 7000 to 10,000 steps walked per day [7,8]. In addition, muscular strengthening PA on at least two days per week is recommended to achieve the health benefits mentioned earlier and reduce the risks of chronic diseases (and the associated cost-intensive curative and rehabilitative measures) [6]. Furthermore, Rütten and Pfeifer [9] emphasize in the German national PA recommendations that adults should also avoid long, uninterrupted sitting phases and, if possible, interrupt sitting regularly with PA. According to the authors, “the greatest health benefits take place when individuals who were entirely physically inactive become somewhat more active. This means that all additional PA is linked to health benefits. Every single step away from physical inactivity is important, no matter how small, and promotes health” [9]. Currently, in Germany, only 43% of women and 48% of men aged ≥18 years meet the WHO and American College of Sports Medicine recommendations for PA [10], highlighting the need for population-based intervention approaches to promote daily PA.

The results of a meta-analysis suggest that engaging in population-based PA intervention approaches recommending the use of step counters to individuals is associated with an increase of approximately 2,000 steps per day [11]. The increase in step count is most pronounced among individuals participating in interventions aimed at promoting 10,000 steps per day [11]. Further, short-term pedometer walking interventions in primary care were associated with health benefits, such as fewer new cardiovascular events and fractures 4 years later [12]. In addition, a review and meta-analysis by Wahlich et al [13], including 9 studies in the review and 5 in the meta-analyses with follow-ups ranging from 12 months to 4 years (age range 18-89 years), revealed increases in steps per day at 12 months for intervention group participants compared with control group participants (mean difference 554, 95% CI 384-724 steps). There is also evidence of sustained intervention effects beyond 1 year. For the 2 outcomes, steps per day and minutes spent with moderate to vigorous PA (MVPA), maintained intervention effects for up to 4 years have been previously demonstrated [13].

Furthermore, previous research suggests that combining individual-level step-count monitoring interventions with environmental approaches to promote PA at the community level, such as signage in parks and other green spaces and media campaigns, in complex intervention approaches leads to increased PA at the population level [14,15]. De Cocker et al [14] implemented a multistrategy community-based intervention aimed at promoting PA in adults aged ≥18 years, which was an adaptation of the “10,000 steps Rockhampton” (Queensland, Australia) program [16,17]. This complex intervention consisted of a website to track steps, a local media campaign, environmental modifications, and the sale and loan of pedometers. Intervention effects were examined in a controlled intervention trial comparing PA at baseline and after 1 year in 872 randomly selected participants (aged 25-75 years) from an entire city (Ghent, Belgium) to 810 living in a comparison city (Aalst, Belgium) [14]. In this study, an increase of 8% in the number of individuals reaching the recommended 10,000 steps was observed in the intervention city at the 1-year follow-up compared with no increase in the comparison city. The average number of daily steps walked increased by 896 (n=660; 95% CI 599-1192) in the intervention compared with no increase in the comparison city (n=634; mean change −135; 95% CI −432 to 162). Self-reported PA confirmed this result.

A 4-year follow-up assessment of self-reported PA in 866 participants in the original trial revealed that daily step counts increased slightly in the intervention city and decreased in the comparison city. Interestingly, subgroup analyses yielded a positive interaction effect for healthier individuals and those with higher levels of education and a negative interaction effect for individuals with poor to moderate health. Thus, long-term intervention effects could not be detected at the 4-year follow-up in individuals living in the intervention city, but decreases in PA, which had been observed in the control group at the 1-year follow-up, could be prevented, except for the subgroup with poor to moderate health [15]. An evaluation of the statewide rollout of the PA intervention in Flanders compared a random sample of adults aged 25 to 75 years (n=881) with a historical control group including the baseline data of participants of both intervention and control groups of the original “10.000 Steps Ghent” intervention (n=1675). Dubuy et al [18] showed that the Flemish sample reported more walking, moderate and vigorous PA, as well as more work-related, leisure time, and household PA compared with the historical control group. In addition, the pedometer-based daily step count was higher, and a greater proportion of Flemish individuals reached the goal of 10,000 steps per day, leading the authors of the study to the conclusion that statewide socioecological complex intervention approaches can impact PA in a large population [18].

Rütten and Pfeifer [9] formulated a need for similar local and regional population-based approaches for PA promotion in Germany, pointing out that complex interventions for PA promotion, including mass media campaigns, motivational decision aids, community-based multicomponent interventions, and environmental approaches, can effectively increase PA in the general population. Thus far, 5 large German research networks (Physical Activity and Health Equity: Primary Prevention for Healthy Ageing [AEQUIPA], CAPITAL4HEALTH, Health Literacy in Childhood and Adolescence [HLCA], PartKommPlus, and SMARTACT) have been working toward improving evidence-based health promotion and primary prevention in Germany, some of them with a special focus on population-based approaches for the promotion of PA [19]. For example, the Physical Activity and Health Equity: Primary Prevention for Healthy Ageing (AEQUIPA) research network [20] conducted theory-based and participatory empirical research on different aspects of PA and healthy aging between the years 2014 and 2022 [20]. In the PROMOTE subproject of the network, multicomponent web- and print-based interventions for the promotion of PA in adults aged ≥60 years were designed following a participatory approach. They were subsequently evaluated with varying follow-ups [21-25], and intervention content and materials are publicly available for adaptation and use in future interventions [26,27].

However, additional studies are still required to strengthen the evidence base regarding effective multilevel approaches for PA promotion in a broad segment of the German population spanning a wide age range. In addition, the implementation processes involved need to be better understood. Replicating the effects of complex interventions for PA promotion, previously shown to be effective in other European countries, may help identify effective intervention strategies for the German context. Therefore, the 2 aims of this study are to adapt the previously shown to be effective complex PA intervention “10,000 Steps Ghent” to the German context (name of the German intervention: “10,000 Steps Duesseldorf”) and to evaluate its effectiveness for PA promotion in adults aged 25 to 75 years over the course of 1 year in 2 German cities in a controlled intervention study. The impact evaluation of the intervention is accompanied by a process evaluation monitoring implementation process as well as an economic evaluation, including cost-effectiveness and cost-utility analyses of the intervention. The specific research questions posed are as follows:

Is the intervention “10,000 Steps Ghent” adaptable and transferrable to the context of city districts in the state of North Rhine-Westphalia?Is the intervention “10,000 Steps Duesseldorf” effective for the promotion of PA among residents of the districts involved?Do individuals located in the city that the intervention is implemented in (Duesseldorf) engage in more PA compared with individuals located in the control city (Wuppertal) after 1 year? Does the absolute number of steps taken per week increase more for individuals residing in the intervention city than in the control city?Does the proportion of those achieving the PA goal of 10,000 steps increase more in the intervention than in the control city after 1 year of potentially being able to participate in intervention activities?To what extent can these differences be attributed to the adoption, implementation, and maintenance of the intervention in the intervention city compared with the control city?What are the costs associated with the provision of the intervention? Does the intervention affect health care use and indirect costs? Is the intervention cost-effective in terms of additional costs per additional person who achieves the PA goal of 10,000 steps and additional costs per additional quality-adjusted life year (QALY) gained compared between the intervention and control cities after 1 year of potentially being able to participate in intervention activities?

## Methods

### Selection of Intervention and Control City Districts, Participants, and Procedures

The effectiveness of the community-based intervention for the promotion of PA is examined over the course of 1 year in a controlled intervention study. The PA behavior of individuals aged 25 to 75 years residing in the intervention districts of the city of Duesseldorf will be compared with that of individuals residing in the respective control districts of the city of Wuppertal at baseline and 1 year. Random samples were drawn based on data from the respective residents’ registration offices. As the size of the cities in North Rhine-Westphalia did not permit an assessment of all residents living in both cities, as was done in the original study [14], adjacent city districts were selected that encompass a similar number of residents as the cities included in the original study. Publicly available information on the levels of socio-spatial deprivation of the districts of Duesseldorf and Wuppertal was used [28,29] during the selection process to ensure a composition of districts balanced by the proportions of residents living in them. The socio-spatial deprivation index is composed of indicators, such as welfare benefits, living space per person, and migrant population. In Duesseldorf, the index ranges from 1 (no deprivation) to 5 (high deprivation), and in Wuppertal, the index ranges from 1 (no deprivation) to 4 (high deprivation). Corresponding to the heterogeneous population of the original study, the Duesseldorf districts of Flingern Nord, Flingern Sued, Oberbilk, Friedrichstadt, Gerresheim, Eller, and Wersten and the Wuppertal districts of Elberfeld and Barmen were chosen. The selected areas and districts in the 2 cities are shown in Figure 1 [30].

**Figure 1 figure1:**
[figure not shown]
Intervention and control city district areas (left, source: Jugendamt Landeshauptstadt Düsseldorf [Youth Welfare Office, State capital Duesseldorf]; right, source: Offene Daten Wuppertal [30]).

### Sampling

On March 1, 2021, a random sample of 2500 residents (25-75 years) based on postal codes (500 individuals per age group: 25-35, 36-45, 46-55, 56-65, and 66-75 years) was drawn for the Duesseldorf districts of Flingern Nord, Flingern Sued, Oberbilk, Friedrichstadt, Gerresheim, Eller, and Wersten, and 2500 residents, using the same distribution, were sampled for the Wuppertal districts of Elberfeld and Barmen. Equal proportions of men and women were included. Thus, the overarching setting in this study is the respective city district in both cities, and the subordinate settings for the implementation of the complex intervention are the organizations located in these districts (eg, senior citizen associations, sports clubs, and companies), as well as the public spaces located in them (eg, parks and green spaces).

### Recruitment

Recruitment for the study was conducted from mid-May to the end of December 2021. Individuals were informed about the study and invited to participate in it via mail. The study information, including information on data protection and the consent form (Multimedia Appendix 1), was provided in the mailed letters. Individuals interested in participating in the study were asked to return the signed consent form (and keep one for their records) and a form, including their telephone number, to the study team in the mail. Alternatively, they could contact the study team directly to make an appointment for the baseline interview and return the signed consent form after the completion of the telephone interview. However, in that case, verbal consent was provided by participants at the beginning of the telephone-based interview. In total, 3 invitation letters were sent to potential participants, and 2 reminder letters were sent 3 and 6 weeks after the first invitation letter. Once contact information was provided by a potential participant, up to 4 phone calls were made to reach the person and schedule an appointment for the baseline interview.

Owing to the COVID-19 pandemic, we expected the response rate to be extraordinarily low. To ensure that we reached the required sample sizes in both cities, a second random sample of another 4000 residents (2,000 in each city) was randomly drawn in both cities and with the same age and gender composition on July 29, 2021. During the second wave of recruitment, only 1 invitation and 1 reminder letter 4 weeks later were sent. Individuals were included in the study if they were (1) between the ages of 25 and 75 years, (2) able to understand German, and (3) residing in Duesseldorf or Wuppertal.

The baseline assessments started at the end of May 2021 and were completed at the end of March 2022. Baseline assessment entails a questionnaire completed by participants over the phone. Two study nurses and 4 student assistants underwent structured training to conduct the 1-hour telephone interviews. Data entry is done simultaneously to the interview over the secured web application, REDCap (Research Electronic Data Capture; Vanderbilt University). The respective REDCap study database is hosted at the Institute for Biometrics and Epidemiology at the German Diabetes Center Duesseldorf and is part of the regular Institute for Biometrics and Epidemiology at the German Diabetes Center IT environment with respect to data security and backups. After the interview, study participants are asked to track their PA over 7 consecutive days using the YAMAX EX210 pedometer, which records daily number of steps. In addition, they are asked to complete a wear-time diary to document the steps walked every day, the times the pedometer was worn, and the possible reasons for not wearing it. After 7 days, participants return the pedometer to the study team via mail, using a stamped return envelope provided by the study team. To validate the pedometer data, a subsample of approximately 30% of study participants receives an accelerometer (ActiGraph wCT3X-BT; ActiGraph LLC) in addition to the pedometer, which they are asked to return in a stamped return envelope after 7 days of wear time. The intervention is being implemented in Duesseldorf for 1 year since April 2022, and follow-up assessments will be conducted, starting in May 2023. The same participants who participated in the baseline assessments will be contacted again via mail, invited to participate in the telephone-based interviews again, and asked to wear pedometers (and accelerometers) for 1 week afterward. To ensure confidentiality, all person-related data assessed in this study will be pseudonymized; that is, all study participants will be assigned an ID number. The roster with the names and ID numbers will be saved in a password-protected file on the server of the Institute of Medical Sociology. The data will be stored for 10 years after the completion of the trial and deleted afterward.

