### Health Economic Evaluation

The health economic evaluation will include a cost-effectiveness analysis (CEA) and a cost-utility analysis from a societal perspective. An incremental cost-efficacy ratio (ICER; additional costs per additional person walking 10,000 steps/day) and an incremental cost-utility ratio (ICUR; additional cost for an additional QALY gained) will be determined. The outcome of the CEA is based on the primary outcome of the intervention and will be taken from the step counter measurement. QALYs will be calculated based on the EQ-5D-5L [44], which is a widely used standardized instrument to assess health-related quality of life. The EQ-5D-5L is evaluated using a German tariff to obtain preference weights [55]. As the intervention might influence people beyond health, we will also consider capability well-being using the ICEpop CAPability measure for adults (ICECAP-A) [48]. We will use a UK scoring tariff because a German tariff does not exist yet [56] and compare utilities based on capabilities with those based on QALYs.

The costs considered in the health economic evaluation comprise costs related to the development and provision of the intervention (eg, print-based materials, website, and time associated with the development of the intervention as opportunity costs), health care use (physician’s visits, contact with therapists, hospital stays, and rehabilitation), and costs associated with PA behavior (devices to support PA, membership fees [eg, gym membership], disability to work, and patient time). Productivity loss due to disability to work is calculated based on the human capital approach [57]. In a sensitivity analysis, patient time associated with PA, evaluated via opportunity costs, will also be examined. A discounting of costs and outcomes is not planned because of the short study duration.

The analysis will be performed according to the intention-to-treat principle. In the base case analysis, missing values will be imputed via multiple imputation. To make the random samples from the intervention and control region comparable, propensity score matching in the form of a weighted regression model will be applied after the imputation and for each imputed data set as suggested by Al-Janabi et al [58]. Covariates used for the matching will be the number of steps taken at baseline, age, gender, level of education, and household income.

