## Results

Funding for this study was obtained in March 2020. Recruitment for this study and baseline data collection were conducted from May 2021 to March 2022 (as of March 2022, 626 participants were enrolled in the study). The intervention is being implemented in Duesseldorf for 1 year from April 2022 onward, and follow-up assessments will be conducted, starting in May 2023 (until September 2023). Data analysis will be performed in fall 2023, and the results will be published in spring 2024.

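### The two step measurements lie 13–28 months apart, not 1 year, and follow-up covers only part of the baseline seasons; the between-city contrast is exposed only if assessment dates or seasonal effects differ by city

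*Protocol article*

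**What the plan says.** **Timing.** On baseline, Recruitment says "The baseline assessments started at the end of May 2021 and were completed at the end of March 2022". On the campaign it says "The intervention is being implemented in Duesseldorf for 1 year since April 2022". The Results section adds that "follow-up assessments will be conducted, starting in May 2023 (until September 2023"). It is one cohort measured twice: "The same participants who participated in the baseline assessments will be contacted again via mail". Each measurement is a single 7-day pedometer week.

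**Label.** The abstract describes the two samples as measured at a 1-year distance ("n=399 in each city) at baseline and after 1 year"). The section on selecting districts says that activity in the intervention districts "will be compared with that of individuals residing in the respective control districts of the city of Wuppertal at baseline and 1 year".

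**Adjustment.** Statistical Analyses plans a comparison of the two groups using matching weights. The covariates of that propensity model are in Multimedia Appendix 2, which is not shown. For the economic analysis the list is printed: "Covariates used for the matching will be the number of steps taken at baseline, age, gender, level of education, and household income". It contains no date or season.

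**Pandemic.** Strengths and Limitations names it as a recruitment difficulty. Tables 1 and 2 include self-report items at both time points on pandemic-related changes in work and activity.

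**The concern.** Baseline runs through summer, autumn and winter of 2021/22, under pandemic conditions. Follow-up falls in late spring and summer 2023. If daily steps vary with season, a person first measured in January and again in July would show a rise that owes nothing to the campaign. With only one week per time point, nothing averages this out within a person.

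Three things are at stake:
- The 1-year label does not describe the interval between measurements.
- Anticipated Principal Findings cites the Ghent result (+896 steps in the intervention city, no increase in the comparison city). A rise within Duesseldorf alone, set beside +896, could be partly seasonal.
- Matching on raw baseline steps, as in the economic model, treats a winter count and a summer count of the same size as equivalent. If the cities differ in when people were measured, the weights carry that difference into the contrast.

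**Working it through.** **1. The plan's yardstick.** The effect size used below is the 1000-step minimal relevant effect from Sample Size Calculation. With SD 4500, two-sided 5% and 80% power, the exact t-test calculation gives 319 per group, 638 in total (power 0.800), matching the stated figure. The point does not depend on the 638; it only borrows the 1000 steps.

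**2. Interval between measurements.** Take the ends of the stated windows as 31 May 2021, 31 March 2022, 1 May 2023 and 30 September 2023, at 30.44 days per month.

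| Pairing | Days | Months |
|---|---|---|
| Last baseline to first follow-up (shortest) | 396 | 13.0 |
| Last baseline to last follow-up | 548 | 18.0 |
| First baseline to first follow-up | 700 | 23.0 |
| First baseline to last follow-up (longest) | 852 | 28.0 |

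No pairing gives 12 months. If follow-up ran in order of enrolment, gaps would run from about 23–24 months (first enrolled) down to about 18 (last enrolled).

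**3. Position relative to the campaign.** From 1 April 2022, follow-up falls 13.0 to 18.0 months after the start, so about 1–6 months after the intervention year ends.

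**4. Seasonal overlap.** The baseline window is 304 days. The part from October to March is 182 days, and 182/304 = 0.60. This is a share of the calendar, not of participants; the article does not say how baselines were spread over the window.

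**5. Effect on a within-city change.** The shift equals the swing times the share of off-season baselines. The documents give no seasonal figure, so assume a summer–winter swing of 500–1500 steps/day. If half of the baselines were off-season, the shift is 0.5 × (500 to 1500) = 250 to 750 steps.

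**6. Effect on the between-city contrast.** For a change score, the bias equals the swing times the difference between cities in the off-season share:

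| Difference in share | Bias (steps/day) | As % of 1000 |
|---|---|---|
| 0 | 0 | 0 |
| 10 points | 50–150 | 5–15 |
| 20 points | 100–300 | 10–30 |
| 30 points | 150–450 | 15–45 |

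The sign depends on which city has more off-season baselines. If the outcome is the follow-up count alone, baseline season does not shift it directly. It then acts only through baseline steps as an adjuster, while an imbalance in follow-up dates within May–September would act directly.

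**7. Noise in the adjuster.** If 60% of participants were measured off-season, the SD of baseline steps would rise from 4500 to √(4500² + 0.6 × 0.4 × swing²), that is 4507 at a swing of 500 and 4560 at 1500. The loss of precision is small; imbalance in dates is the main issue.

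**The case against.** The strongest reply is that the concurrent control city exists to absorb calendar effects. Both cities share the baseline and follow-up windows. Sampling was parallel: 2500 residents per city in the first draw and 2000 per city in the second, with the same age and gender composition and no city-specific mailing schedule described. If dates are distributed alike and season acts alike, the between-city bias is zero. The research questions ask whether steps increase more in one city than in the other, and the planned analysis compares the groups. This stands. Parallel mailing does not guarantee equal dates, because appointments followed individual response, but the article gives no evidence of an imbalance.

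A reader might infer that the primary model ignores season. The documents do not support that: its covariate list is in an appendix not shown, and the printed list belongs to the economic analysis only.

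It can also be said that 1 year refers to exposure, that the true dates are disclosed, and that 28 months would require the first person enrolled to be followed up last. All fair. Still, the abstract and the section on selecting districts attach the label to the measurements, and even the shortest gap is 13 months. The pandemic items capture part of the recovery effect, but the article does not link them to the step analysis.

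**Conclusion.** The dates and the interval are certain. Measurements lie 13–28 months apart, follow-up is 13–18 months after campaign start, and about 60% of the baseline calendar has no matching follow-up months. Two statements of a 1-year measurement interval need correcting. Changes within a city may mix season and pandemic recovery with any effect.

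The stronger conclusion, that season and pandemic recovery bias the primary comparison, is not supported. Bias in the between-city contrast requires assessment dates, or the seasonal or pandemic effects themselves, to differ by city. The article does not report the dates by city and states nothing that keeps them balanced at follow-up. The size is therefore unknown: zero with equal timing, and 100–300 steps/day on a change score with a 20-point imbalance and a swing of 500–1500 steps. Both of those inputs are assumptions. The absence of a date or season term can be asserted for the economic model only. The point is a conditional risk that can be guarded against cheaply, together with a factual correction.

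**What to change.** 1. **Scheduling.** Release follow-up invitations in both cities in the same calendar blocks, so that the mix of follow-up weeks is alike. At the article's publication in September 2022 follow-up had not begun, so this was still possible; if it has since run, items 2 and 3 remain.
2. **Models.** Add month or season of the baseline pedometer week to the economic propensity model, and to the primary one if Multimedia Appendix 2 lacks it. Add baseline and follow-up measurement month to the weighted outcome model. A sensitivity analysis restricted to participants with baseline in May–September would show how much season matters.
3. **Wording and reporting.** In the abstract and the section on selecting districts, give the interval as 13–28 months between measurements. Report assessment dates by city. Do not read a within-city change set against the Ghent +896 as an intervention effect.

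The cost is some scheduling effort and a few degrees of freedom. No new measurement is needed, provided the date of each pedometer week is recorded, which is likely given the wear-time diary but not stated.
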